**System Usability Scale**

1. How often did you use the platform in the eight week period?

□ never

□ approximately once a month

□ approximately once a week

□ couple of times a week

□ every day

1. How many minutes did you use the platform approximately per session?

_____________ hours _____________ minutes

[figure not shown]

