**8.5 Participant population**

Any participant who participated in the project will be subjected to statistical or thematic analyses, except for participants who withdraw from the project before data gets anonymized. This date will be explicitly mentioned in the Participant Information and will be two weeks after data collection took place. Moreover, participants who did not opt-in for their platform usage data to be shared with CU lead researchers upon referral to the platform through Diabetes UK will not be subject to statistical analyses and labelled as missing data.

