**Diabetes Related Health Status**

1. We would like to know your height. Would you like to answer in imperial (feet, inches) or metric (metres, centimetres) units? Please specify date DD/MM/YYYY.

□ Imperial (feet, inches)

□ Metric (metres, centimetres)

[Based on answer skip to drop down menus to select height in preferred units]

1. **How was this height measured:** (if other please specify)

□ Myself

□ Doctor

□ Other, please specify_________________________

□ Don’t know

□ Prefer not to say

1. We would like to know your weight. Would you like to answer in imperial (stones, pounds) or metric (kilograms) units? Please specify date DD/MM/YYYY.

□ Imperial (stones and pounds)

□ Metric (kilograms)

[Based on answer skip to drop down menus to select weight in preferred units]

1. **How was this weight measured:** (if other please specify)

□ Myself

□ Doctor

□ Other, please specify_________________________

□ Don’t know

□ Prefer not to say

1. We would like to know your waist size. Would you prefer to answer in imperial (inches) or metric units (centimetres)? Please specify date DD/MM/YYYY.

□ Imperial (inches)

□ Metric (centimetres)

[Based on answer skip to drop down menus to select waist size in preferred units]

[figure not shown]
Above the belly button, just below the rib cage. Bend to one side to find natural crease of your waist. Measure across at this point.

1. **How was this waist size measured:** (if other please specify)

□ Myself

□ Doctor

□ Other, please specify_________________________

□ Don’t know

□ Prefer not to say

1. What is your most recent blood glucose (sugar) level? (HbA1c mmol/mol)

□ Don’t know

□ Prefer not to say

1. What is the date of your most recent blood glucose level measurement?

DD/MM/YYYY

□ Don’t know

□ Prefer not to say

1. What is your most recent blood pressure level?

Systolic (top number) mmHg [drop down menu – 70, 80, 90, 100, 110, 120, 130, 140, 150, 160, 170, 180, 190]

Diastolic (bottom number) mmHg [drop down menu – 40, 50, 60, 70, 80, 90, 100]

□ Don’t know

□ Prefer not to say

1. What was the date of your most recent blood pressure level?

DD/MM/YY

□ Don’t know

□ Prefer not to say

1. What was your most recent HDL cholesterol level (mmol/L)?

[drop down menu]

□ Don’t know

□ Prefer not to say

1. What was your most recent TOTAL cholesterol level?

______________ mmol/L [drop down menu]

□ Don’t know

□ Prefer not to say

1. What is the date of your most recent cholesterol measurement?

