**Confidence regarding diabetes management and meal planning**

1. The platform made me feel more confident in managing my diabetes

| 1 – Very strongly disagree | 2 | 3 | 4 | 5 – Neither agree nor disagree | 6 | 7 | 8 | 9 | 10 – Very strongly agree |
| --- | --- | --- | --- | --- | --- | --- | --- | --- | --- |
|  |  |  |  |  |  |  |  |  |  |

1. After using the platform, I felt more confident in making healthy food choices

| 1 – Very strongly disagree | 2 | 3 | 4 | 5 – Neither agree nor disagree | 6 | 7 | 8 | 9 | 10 – Very strongly agree |
| --- | --- | --- | --- | --- | --- | --- | --- | --- | --- |
|  |  |  |  |  |  |  |  |  |  |

1. After using the platform, I feel more confident planning meals

| 1 – Very unconfident | 2 | 3 | 4 | 5 – Neither confident nor unconfident | 6 | 7 | 8 | 9 | 10 – Very confident |
| --- | --- | --- | --- | --- | --- | --- | --- | --- | --- |
|  |  |  |  |  |  |  |  |  |  |

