**Satisfaction**

1. The platform supported me in diabetes management

| 1 – Very Strongly disagree | 2 | 3 | 4 | 5 – Neither agree nor disagree | 6 | 7 | 8 | 9 | 10 – Very strongly agree |
| --- | --- | --- | --- | --- | --- | --- | --- | --- | --- |
|  |  |  |  |  |  |  |  |  |  |

Please explain your rating _________________________

1. The platform supported me in making healthy food choices?

| 1 – Very Strongly disagree | 2 | 3 | 4 | 5 – Neither agree nor disagree | 6 | 7 | 8 | 9 | 10 – Very strongly agree |
| --- | --- | --- | --- | --- | --- | --- | --- | --- | --- |
|  |  |  |  |  |  |  |  |  |  |

Please explain your rating _________________________

1. The platform supported me in planning my meals more efficiently and within budget?

| 1 – Very Strongly disagree | 2 | 3 | 4 | 5 – Neither agree nor disagree | 6 | 7 | 8 | 9 | 10 – Very strongly agree |
| --- | --- | --- | --- | --- | --- | --- | --- | --- | --- |
|  |  |  |  |  |  |  |  |  |  |

Please explain your rating _________________________

1. The platform supported me in my food shopping experience?

| 1 – Very Strongly disagree | 2 | 3 | 4 | 5 – Neither agree nor disagree | 6 | 7 | 8 | 9 | 10 – Very strongly agree |
| --- | --- | --- | --- | --- | --- | --- | --- | --- | --- |
|  |  |  |  |  |  |  |  |  |  |

Please explain your rating _________________________

5. Did the platform teach you anything else, apart from what is mentioned above?

□ Yes, please explain your answer _________________________

□ No, please explain your answer _________________________

6. Are there any features of this platform that you particularly liked?

□ Yes, please explain your answer _________________________

□ No, please explain your answer _________________________

7. Are there any features of this platform that you particularly disliked?

□ Yes, please explain your answer _________________________

□ No, please explain your answer _________________________

8. Did you encounter any technical problems?

□ Yes, please explain your answer _________________________

□ No, please explain your answer _________________________

9. The platform is a valuable addition to the Diabetes UK learning environment?

| 1 – Very Strongly disagree | 2 | 3 | 4 | 5 – Neither agree nor disagree | 6 | 7 | 8 | 9 | 10 – Very strongly agree |
| --- | --- | --- | --- | --- | --- | --- | --- | --- | --- |
|  |  |  |  |  |  |  |  |  |  |

Please explain your rating _________________________

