10. The platform is easy to use / user-friendly

| 1 – Very Strongly disagree | 2 | 3 | 4 | 5 – Neither agree nor disagree | 6 | 7 | 8 | 9 | 10 – Very strongly agree |
| --- | --- | --- | --- | --- | --- | --- | --- | --- | --- |
|  |  |  |  |  |  |  |  |  |  |

Please explain your rating _________________________

11. Would you recommend the platform to other people who have Diabetes or are taking care of people with Diabetes?

□ Yes, please explain your answer _________________________

□ No, please explain your answer _________________________

12. How motivated were you to use the platform?

| 1 – Not very motivated | 2 | 3 | 4 | 5 – Neither unmotivated nor motivated | 6 | 7 | 8 | 9 | 10 – Very motivated |
| --- | --- | --- | --- | --- | --- | --- | --- | --- | --- |
|  |  |  |  |  |  |  |  |  |  |

Please explain your rating _________________________

13. Based on your experience, how would you rate the platform overall? (1=not good at all, 10 = very good)

| 1 | 2 | 3 | 4 | 5 | 6 | 7 | 8 | 9 | 10 |
| --- | --- | --- | --- | --- | --- | --- | --- | --- | --- |
|  |  |  |  |  |  |  |  |  |  |

14. Would you like to continue using the platform?

□ Yes, please explain your answer _________________________

□ No, please explain your answer _________________________

15. Do you think COVID-19 restrictions have been affecting optimal usage of the platform?

□ Yes, please explain your answer _________________________

□ No, please explain your answer _________________________

16. What would you improve to the platform?

………………………………………………………………………………………………………………………………………………………………………………………………………………………………………………………………………………………………………………………………………………………………………………………………............................................................................................................................................................................................................

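### The second survey accepts never as an answer on platform use, but prints no skip or did-not-use option for the ratings that presuppose use, and the analysis plan does not separate never-users

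*Combined protocol and SAP*

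**What the plan says.** Section 7 sends the second survey eight weeks into platform use and describes no check that the person has used it. In Attachment 6 the confidence block comes before the System Usability Scale and Satisfaction blocks.

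- **Use.** The usability block opens with "How often did you use the platform in the eight week period". It has five options, from never to daily. The next item is "How many minutes did you use the platform approximately per session", and after it comes a figure that is not shown.
- **Ratings.** The Satisfaction block asks for 1-10 ratings, among them "The platform supported me in diabetes management", "The platform is easy to use / user-friendly" and "Based on your experience, how would you rate the platform overall". None shows a not-applicable answer.
- **Confidence.** Ahead of the use question, respondents meet items such as "After using the platform, I felt more confident in making healthy food choices", again on 1-10 scales.
- **Routing.** Where the survey branches on units, it prints the instruction: "Based on answer skip to drop down menus to select height in preferred units", with matching notes for weight and waist.

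On analysis, Section 8.5 says "Any participant who participated in the project will be subjected to statistical or thematic analyses", apart from people who withdraw before anonymisation. Its only other rule concerns people who did not agree to share usage data. Section 8.3.2 describes survey results by sociodemographic characteristics. It relates platform usage to health outcomes where possible, but not to the ratings. Section 8.6, on missing or spurious data, deals only with interview recordings and withdrawal.

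**The concern.** A rating of 5 from a user means indifference. The same 5 from someone who did not use the platform carries no information about it. Likewise, a never-user who reports no technical problem is not evidence that the platform works reliably.

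Objective 3 in Section 3.1 rests on usability and user experience, and Section 1 ties the results to a business-case decision. Confidence in diabetes management and meal planning is also listed among the primary outcomes in Section 3.2, so the earlier confidence block matters as much as the satisfaction block.

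Section 8.4 plans comparisons by digital literacy, age and other characteristics. If non-use differs between those groups, a difference in uptake could show up as a difference in satisfaction.

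**Working it through.** The plan states no figure on this point, so there is nothing to reproduce. The check has two parts.

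**1. Survey flow against analysis rules**

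- Never-users can reach the ratings. Entry needs sign-up (Section 7), and the second invitation is not described as conditional on use. The never option shows that such respondents were foreseen.
- No routing is printed where it is needed. The attachment prints routing for height, weight and waist, and Attachment 4 prints a conditional follow-up on long-standing illness. Its absence after the use question is therefore informative, though not conclusive.
- A skip placed at the use question would come too late for the confidence items, which have already been shown.
- No rule in 8.3.2, 8.5 or 8.6 separates or excludes the ratings of people who answer never.

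**2. Possible size (all inputs assumed)**

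Let q be the share of raters who answered never, U the mean among users and N the mean among never-users.

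Pooled mean = (1 - q) x U + q x N, so the shift from the users' mean is q x (N - U).

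| q | U = 8, N = 5 | U = 7, N = 5 | U = 8, N = 1 | U = 7, N = 1 |
|---|---|---|---|---|
| 5% | -0.15 | -0.1 | -0.35 | -0.3 |
| 10% | -0.3 | -0.2 | -0.7 | -0.6 |
| 20% | -0.6 | -0.4 | -1.4 | -1.2 |
| 30% | -0.9 | -0.6 | -2.1 | -1.8 |

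Example: q = 20%, U = 8, N = 5 gives 0.8 x 8 + 0.2 x 5 = 7.4, a shift of -0.6.

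The shift depends on q and not on the number of respondents. Its sign follows N - U, so it would be upward if never-users rated higher than users.

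Subgroup illustration: take two groups whose users both average 8, with never-users at 5. If 5% of one group and 20% of the other are never-users, the pooled means are 7.85 and 7.4. That is a gap of 0.45 with no difference in users' experience.

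**Effect of the fix on the denominator.** With the anticipated 200 to 300 survey respondents (Section 8.1), q of 5%, 10%, 20% and 30% leaves 190, 180, 160 and 140 users of 200, or 285, 270, 240 and 210 of 300.

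**The case against.** Four stronger readings are tempting, and the documents support none of them.

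- **Never-users are forced to rate.** No section says that items are mandatory. Attachment 6 asks respondents only to complete as much as they can, so some may leave ratings blank or use the free-text explanation.
- **The plan pools their answers.** Section 8.5 says whose data are analysed and sets no denominator for any item. Pooling is an inference from the absence of a rule. A skip could also be programmed in the survey software without being printed.
- **The System Usability Scale has no skip.** Its items are probably in the figure that is not shown, so this cannot be checked.
- **Never-users have not seen the platform.** They signed up for it (Section 7), and the question covers the eight-week period. Section 7.5.4 also foresees people who print recipes at first login and do not return.

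It can further be argued that the stakes are modest. The project is exploratory with no hypotheses, no threshold rests on these scores, and Objective 3 also draws on usage data and interviews, some with people chosen for low engagement. Never-users who return both surveys may be few. The answer on use is recorded, so an analyst could filter later.

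Much of this stands, and it limits the point to what the printed text shows. Later filtering is only a partial answer. No section commits to it, and it leaves the choice of denominator until after the scores are seen. It also cannot recover reasons for non-use, which no dedicated item asks.

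**Conclusion.** The point holds in a limited form. The printed second survey lets a person report never using the platform and then shows ratings that presuppose use. It has already shown confidence items that do the same. Nothing in Sections 8.3.2 or 8.5 keeps those answers out of the platform's scores.

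This rests on the text of the confidence and satisfaction blocks and does not depend on the unseen usability items. It assumes that the attachment reflects the survey as fielded.

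The size is unknown. With a user mean of 8 and neutral answers from never-users, the mean falls by 0.15 to 0.9 points for shares of 5% to 30%. All of these inputs are assumptions. This is an inexpensive improvement to the instrument and the reporting rule. It does not show that the scores are biased by any given amount.

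**What to change.** **In Attachment 6**

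- Move the use question ahead of the confidence section.
- For respondents who answer never, skip only the items that presuppose use, or add a did-not-use option to them. These are the confidence-since-use items, minutes per session, the System Usability Scale, the support, ease-of-use and overall ratings, and features liked or disliked.
- Keep technical problems, motivation, COVID-19, continuing use and improvements open to everyone. A technical fault may be the reason for non-use.
- Decide explicitly where Satisfaction items 5, 9 and 11 belong (other learning, value to the Diabetes UK environment, recommendation).
- Add one item on the reason for non-use.

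**In Section 8.3.2**

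- State that usability, satisfaction and confidence-since-use scores are reported among self-reported users, with the number and percentage of never-users beside them.
- State that self-report defines use for this purpose. Section 7.5.4 notes that tracked usage can miss printed recipes, and Section 7 lets people answer the surveys without sharing usage data.
- Keep never-users in the before/after health comparison.

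**Cost.** One moved item, one display rule, one added item and a few sentences in 8.3.2. The ratings have a slightly smaller denominator.

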**Satisfaction**

1. The platform supported me in diabetes management

| 1 – Very Strongly disagree | 2 | 3 | 4 | 5 – Neither agree nor disagree | 6 | 7 | 8 | 9 | 10 – Very strongly agree |
| --- | --- | --- | --- | --- | --- | --- | --- | --- | --- |
|  |  |  |  |  |  |  |  |  |  |

Please explain your rating _________________________

1. The platform supported me in making healthy food choices?

| 1 – Very Strongly disagree | 2 | 3 | 4 | 5 – Neither agree nor disagree | 6 | 7 | 8 | 9 | 10 – Very strongly agree |
| --- | --- | --- | --- | --- | --- | --- | --- | --- | --- |
|  |  |  |  |  |  |  |  |  |  |

Please explain your rating _________________________

1. The platform supported me in planning my meals more efficiently and within budget?

| 1 – Very Strongly disagree | 2 | 3 | 4 | 5 – Neither agree nor disagree | 6 | 7 | 8 | 9 | 10 – Very strongly agree |
| --- | --- | --- | --- | --- | --- | --- | --- | --- | --- |
|  |  |  |  |  |  |  |  |  |  |

Please explain your rating _________________________

1. The platform supported me in my food shopping experience?

| 1 – Very Strongly disagree | 2 | 3 | 4 | 5 – Neither agree nor disagree | 6 | 7 | 8 | 9 | 10 – Very strongly agree |
| --- | --- | --- | --- | --- | --- | --- | --- | --- | --- |
|  |  |  |  |  |  |  |  |  |  |

Please explain your rating _________________________

5. Did the platform teach you anything else, apart from what is mentioned above?

□ Yes, please explain your answer _________________________

□ No, please explain your answer _________________________

6. Are there any features of this platform that you particularly liked?

□ Yes, please explain your answer _________________________

□ No, please explain your answer _________________________

7. Are there any features of this platform that you particularly disliked?

□ Yes, please explain your answer _________________________

□ No, please explain your answer _________________________

8. Did you encounter any technical problems?

□ Yes, please explain your answer _________________________

□ No, please explain your answer _________________________

9. The platform is a valuable addition to the Diabetes UK learning environment?

| 1 – Very Strongly disagree | 2 | 3 | 4 | 5 – Neither agree nor disagree | 6 | 7 | 8 | 9 | 10 – Very strongly agree |
| --- | --- | --- | --- | --- | --- | --- | --- | --- | --- |
|  |  |  |  |  |  |  |  |  |  |

Please explain your rating _________________________

10. The platform is easy to use / user-friendly

| 1 – Very Strongly disagree | 2 | 3 | 4 | 5 – Neither agree nor disagree | 6 | 7 | 8 | 9 | 10 – Very strongly agree |
| --- | --- | --- | --- | --- | --- | --- | --- | --- | --- |
|  |  |  |  |  |  |  |  |  |  |

Please explain your rating _________________________

11. Would you recommend the platform to other people who have Diabetes or are taking care of people with Diabetes?

□ Yes, please explain your answer _________________________

□ No, please explain your answer _________________________

12. How motivated were you to use the platform?

| 1 – Not very motivated | 2 | 3 | 4 | 5 – Neither unmotivated nor motivated | 6 | 7 | 8 | 9 | 10 – Very motivated |
| --- | --- | --- | --- | --- | --- | --- | --- | --- | --- |
|  |  |  |  |  |  |  |  |  |  |

Please explain your rating _________________________

13. Based on your experience, how would you rate the platform overall? (1=not good at all, 10 = very good)

| 1 | 2 | 3 | 4 | 5 | 6 | 7 | 8 | 9 | 10 |
| --- | --- | --- | --- | --- | --- | --- | --- | --- | --- |
|  |  |  |  |  |  |  |  |  |  |

14. Would you like to continue using the platform?

□ Yes, please explain your answer _________________________

□ No, please explain your answer _________________________

15. Do you think COVID-19 restrictions have been affecting optimal usage of the platform?

□ Yes, please explain your answer _________________________

□ No, please explain your answer _________________________

16. What would you improve to the platform?

………………………………………………………………………………………………………………………………………………………………………………………………………………………………………………………………………………………………………………………………………………………………………………………………............................................................................................................................................................................................................

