3.2 Primary endpoint/outcome

The primary outcomes are categorized as follows: (1) Outcomes directly related to the health status and condition management of the participants (e.g. weight, BMI, HbA1c, blood pressure, waist, generic health status, smoking yes/no, confidence in diabetes management and meal planning, healthy eating) and (2) Outcomes directly related to platform intervention usage:

- Number / Duration of sessions
- Number of users / average sessions per user
- New users
- Monthly Active Users / Weekly Active Users
- Specific actions:
  - # Recipes Viewed, (any indication on favourite content)
  - # Recipe Added / Saved
  - # Meal Plans created
  - # Shopping Actions
    - Carts sent online
    - Meal plans sent to cart
    - In store shopping actions - print, email, sms, app, etc.
    - Number of items shopped / value
- Platform used - app vs web app
- GA audience metrics: Demographics, Geography,
- User Retention
- Top 20 recipes (potentially)
- The average or typical meal plan including health score (potentially)

Additionally, expectations beforehand and satisfaction afterwards will be assessed. Diabetes UK will collect data regarding their traffic on the website and the amount of referrals to the online platform.

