8.3.2 Primary outcome analysis

Participants will be analysed on health outcomes before and after they used the platform to see if there is an improvement within this group over time. These data will be analysed using IBM SPSS software (version 26) generating descriptive and inferential statistics with reported effect size (if data availability/quality allows). Descriptive data of platform usage (e.g. session frequency, session duration, pages visited, health score for recipes used) will also be provided by the platform developer through Mix panel. These data will be exported into IBM SPSS software (version 26) and will be used to select participants with different engagement levels (low vs. high) for participation in case studies and semi-structured interviews. Where possible descriptive data of platform usage will be related to health outcomes. Results of the case study interviews and semi-structured interviews will be transcribed verbatim and thematically analysed (based on Grounded Theory) resulting in overall key themes. Survey results will be exported to and coded using IBM SPSS software (version 26) and described using descriptive statistics (e.g. frequencies, percentages, medians and means) according to sociodemographic characteristics (e.g. ethnic group, age, digital literacy, educational level, diagnosis and sex).

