**8.4** **Subgroup analyses**

Sub-group (or moderator analyses) according to expectations, age, ethnicity, digital literacy and sex will be conducted to examine possible differences in intervention and health outcomes. Data will be analysed using IBM SPSS Software, generating descriptive and inferential statistics with reported effect size, if data availability/quality allows.

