**Expectations**

1. I think that the platform will help me to manage my diabetes

| 1 – Very Strongly disagree | 2 | 3 | 4 | 5 – Neither agree nor disagree | 6 | 7 | 8 | 9 | 10 – Very strongly agree |
| --- | --- | --- | --- | --- | --- | --- | --- | --- | --- |
|  |  |  |  |  |  |  |  |  |  |

Please explain your rating _________________________

1. The platform will help me to make healthy food choices

| 1 – Very Strongly disagree | 2 | 3 | 4 | 5 – Neither agree nor disagree | 6 | 7 | 8 | 9 | 10 – Very strongly agree |
| --- | --- | --- | --- | --- | --- | --- | --- | --- | --- |
|  |  |  |  |  |  |  |  |  |  |

Please explain your rating _________________________

1. The platform will help me to plan my meals more efficiently

| 1 – Very Strongly disagree | 2 | 3 | 4 | 5 – Neither agree nor disagree | 6 | 7 | 8 | 9 | 10 – Very strongly agree |
| --- | --- | --- | --- | --- | --- | --- | --- | --- | --- |
|  |  |  |  |  |  |  |  |  |  |

Please explain your rating _________________________

1. Using the platform will improve my food shopping experience

| 1 – Very Strongly disagree | 2 | 3 | 4 | 5 – Neither agree nor disagree | 6 | 7 | 8 | 9 | 10 – Very strongly agree |
| --- | --- | --- | --- | --- | --- | --- | --- | --- | --- |
|  |  |  |  |  |  |  |  |  |  |

Please explain your rating _________________________

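### The second-survey meal-planning satisfaction item rates efficiency and budget together, so a low or middle score cannot be attributed to either

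*Combined protocol and SAP*

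**What the plan says.** The first survey (Attachment_4, Expectations) has four agreement items on what the platform will do for the respondent. The third is "The platform will help me to plan my meals more efficiently". The second survey (Attachment_6, Satisfaction), sent after 8 weeks of use, opens with four agreement items on the same topics. The third of these is "The platform supported me in planning my meals more efficiently and within budget", put as a question. Both items use a 1 to 10 scale that starts at "1 – Very Strongly disagree" and has its neutral label at 5. Both are followed by an open box headed "Please explain your rating".

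On use, section 3.2 states: "Additionally, expectations beforehand and satisfaction afterwards will be assessed". Section 8.3.2 says survey results will be "described using descriptive statistics (e.g. frequencies, percentages, medians and means) according to sociodemographic characteristics". Section 8.4 says "Sub-group (or moderator analyses) according to expectations, age, ethnicity, digital literacy and sex will be conducted", with intervention and health outcomes as the targets. Objective 3 in section 3.1 relies partly on the surveys to identify perceived benefits and weaknesses of the platform.

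**The concern.** Planning meals efficiently and staying within a budget are different things, and a user can gain on one while losing on the other. Someone who now plans faster but spends more has no accurate answer on a single scale. Neither has someone who spends less but plans no faster. Each must choose which half to rate or strike some average, and the number does not record which.

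What is at stake is the use of this item under objective 3. Meal planning is one of the two functions that section 1.1 names for the platform, the other being recipes. This is also the only second-survey item on planning efficiency. If its mean is mediocre, the report cannot say whether the planning tool or the cost of the meals needs attention. The same holds for differences between sociodemographic groups, since groups may differ in how much the budget half weighs with them.

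**Working it through.** The documents give no figure for this item and the point rests on wording, so the check is a comparison of the two surveys and the planned analyses.

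**Step 1. Compare the items in order.**

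| Position | Expectation item (Attachment_4) | Satisfaction item (Attachment_6) | Attribute added? |
| --- | --- | --- | --- |
| 1 | Diabetes management | Diabetes management | No |
| 2 | Healthy food choices | Healthy food choices | No |
| 3 | Meal planning: efficiency | Meal planning: efficiency and budget | Yes, budget |
| 4 | Food shopping: will improve it | Food shopping: gave support in it | No, but the verb is weaker |

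Topics, order and response scale agree, so the items read as parallel sets. Only the third pair gains an attribute. The difference is in content, not in scale.

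**Step 2. Look for a separate budget question.** There is none in either survey. Budget otherwise appears only in the case study interview outline (Attachment_10, Changes), which covers four people. That outline lists shopping and budget as one prompt and meal planning as another, so the project's own material treats them as distinct.

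**Step 3. Look for a substitute item on planning.** The confidence block of Attachment_6 asks about meal planning without budget. It concerns confidence rather than efficiency, and it attaches a scale from unconfident to confident to a statement that already says the respondent is more confident. It does not replace the item.

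**Step 4. See what can be read from a score.** A score near 10 suggests agreement with both halves. A low or middle score fits at least three states: poor on efficiency, poor on budget, or poor on both. One number cannot separate them, and neither can a mean or a percentage of such numbers.

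**Step 5. Trace the planned uses.** Sections 3.2 and 7.5.1 say that expectations and satisfaction are assessed. Section 8.3.2 describes survey answers. No section specifies a difference score or a paired test between the two. In sections 7.5.1 and 8.4 expectations act as the moderator, and that variable comes from the first survey, where the item has one attribute. The fault therefore reaches the descriptive report of this item and any informal reading against expectations, and nothing else.

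**The case against.** The strongest reply is that little depends on this item. It is one of 16 satisfaction questions in an evaluation with no hypotheses (section 2) and no statistically derived sample size (section 8.1). Section 3.2 mentions satisfaction after, and outside, its two categories of primary outcome. The open box lets a respondent explain a split view, and section 7.5.3 provides for interviews that explore survey findings further. All of this stands and keeps the point minor. It does not remove the ambiguity: the box is free text that leaves the number unchanged, and the interviews reach about 24 people, some of them staff.

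Four stronger readings are tempting, and the documents do not support them.

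- *The score is uninterpretable.* This goes too far. A high score suggests agreement with both halves, and the free text will clarify some of the others.
- *A planned comparison with expectations is spoiled.* None is planned. The wording "expectations beforehand and satisfaction afterwards will be assessed" and the parallel order invite one, but the item sets are only loosely parallel, as the shopping pair shows.
- *The moderator analysis is compromised.* It uses the first-survey item, which is sound.
- *The score is biased downwards.* The sign is unknown. Assume, for illustration only, that 20% of users find planning easier but dearer and mark 3 points lower because of cost: the mean moves by 0.20 × (−3) = −0.6. If instead 20% spend less but plan no faster and mark 3 points higher, it moves by 0.20 × 3 = +0.6. The documents give no figure that favours either case.

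**Conclusion.** The point holds as a minor wording fault. The item is double-barrelled, its expectation counterpart is not, and budget has no survey item of its own. A low or middle score, summarised as section 8.3.2 intends, cannot be assigned to planning efficiency or to cost. A comparison with the expectation item would mix unmet expectation with an added condition.

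The extent is one satisfaction item. No primary health or usage outcome, paired analysis or moderator analysis depends on it. No numerical size can be given, because the documents do not say how many users would rate the two halves differently or by how much.

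The facts about wording and planned use are read directly from the documents. The one inference is that the two sets of four items were meant to correspond, which rests on their shared topics, order and scale. The double-barrelled fault does not need that inference.

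**What to change.** If the second survey has not yet been sent, end the meal-planning satisfaction item after the efficiency phrase, so that it covers the same attribute as the first-survey item, and ask about support in keeping to a food budget as a separate item on the same scale. The cost is one edit and one extra question within the 20-minute maximum of section 7.5.4. The new budget item will have no expectation counterpart unless a matching one is added to the first survey, which is worth doing only if a comparison is wanted.

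If the data are already collected, report the item as a composite of efficiency and budget, use the free-text explanations to describe which half drove low and middle ratings, and do not compute a change from the expectation item.
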